#### Costs

The cost model will be based on the concept of opportunity cost, that is, the value of the benefit forgone in not employing a resource in a different use. In this analysis, market prices will be used as a proxy for this value. Labour costs will include an overhead to allow for additional costs of employment. Materials refer to non-abour cost items such as stationary (education materials) or electronic hardware or software. Joint costs are defined as those costs incurred in connection with multiple projects. For example, the maintenance costs of a website portal supporting different interventions. Capital costs refer to major one-off investments such as the purchase of additional office buildings or motor vehicles. Miscellaneous costs are considered to be those costs not easily classified into the other categories. The primary outcome from the cost model will be an estimate of the mean cost per school of implementing the intervention. Costs for each of the intervention elements will be reported separately and jointly. The analysis will adhere to cost and economic analysis guidelines [67–69]. To maintain a conservative approach to cost estimation, the non-capital implementation costs are not amortised.

#### Cost consequence analysis

Cost consequence analysis, the listing of all cost/benefit implications of each alternative, represents the simplest form of economic evaluation. In this analysis, where the collection of outcomes is diverse, it has value in being able to inform spending decisions by capturing the range of returns generated by the investment.

#### Cost effectiveness analysis

Subject to assessment of effectiveness, the trial-based evaluation will include assessment of cost-effectiveness. It has been suggested that one of the ways to improve efficiency in conducting economic evaluations of implementation interventions, is to confine the study to measures of the care process or intermediate outcomes [70]. This is the approach adopted in this study, where the cost-effectiveness outcomes, the incremental cost effectiveness ratios (ICER) will be: (i) incremental cost per percent change in the proportion of schools implementing at least four of the seven PA practices, reflective of the primary trial outcome and (ii) incremental cost per unit changes in student-level outcomes (minutes of MVPA per day, % reduction in BMI and metabolic equivalent (MET) hours gained). The ICERs will be calculated as the arithmetic mean difference in cost between the intervention and usual practice arms divided by the arithmetic mean difference in effect [68, 71].

Uncertainty analysis will be conducted using parametric and non-parametric bootstrapping techniques and sensitivity analyses will be conducted to explore the robustness of the economic outcomes to any uncertainty associated with key parameters.

#### Budget impact analysis

A budget impact analysis considers specific requirements of policy makers taking account of local perspective and time horizons. Subject to assessment of effectiveness, the results of the cost and cost-consequence analyses will be reconfigured as a budget impact statement reflecting the costs and outcomes falling directly within specific budgets and within the usual timeframe of the budget holder.

All of the analyses will be constructed in Microsoft Excel and will adhere to international reporting standards for economic evaluations [67].

#### Process data

A mixed methods process evaluation based on Proctor et al. [61] will be undertaken using a descriptive analysis that will be detailed in a separate protocol.

### Sample size

Based on publicly available data there are approximately 120 potentially eligible schools. Based on school consent rates in previous trials conducted by the researchers of around 65–70% [15], a sample of 76 schools (38 per arm) will provide 80% power to detect an absolute increase of ~ 35% between groups in the proportion of schools implementing at least 4 of the 7 items at 12 and 24-months (alpha 0.025 to allow for program effect at 12 or 24 months). Without prior data on baseline levels of school practices, this calculation makes the conservative assumption that 40% of schools in the usual care arm achieve this target at follow-up.

For student level variables it is estimated that a nested sample of 30 schools and a student consent rate of 65% will yield about 1200 students (600 per group) with valid accelerometer data. Using an ICC of 0.03 [15] and a standard deviation of 23 min of MVPA, will allow a 6.2 min [47] difference in the mean difference between groups at each separate follow-up to be detected with 80% power and a 2.5% type 1 error rate.

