### Randomisation

Consenting schools will be randomised to either program or control condition using a random number function in Microsoft Excel. Block randomisation (1:1) will be undertaken within the strata (four local health districts and two school sectors). Principals will be notified of their school allocation following baseline collection of school practice measures. Schools consenting to student level data (nested study) will be randomly selected within strata using a random number generator in Excel, and at stratum sizes proportional to that observed in the main study. Schools will be notified of student level measurement involvement when notified of group allocation.

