#### Primary outcomes

The primary outcome is the proportion of schools implementing at least four of the seven PA practices [47] based on the Head PE teacher computer assisted telephone interview data. The analysis will follow intention-to-treat principles, with multiple imputation the primary method of dealing with missing data. Per protocol analyses will also be performed, based on those schools receiving the full implementation support intervention.

Differences between treatment groups in the primary outcome at 12 and 24-months will be assessed using generalised linear regression models (a separate analysis conducted for each time point). A log link and binomial distribution function will be used (a logistic link will be utilised if the analysis model fails convergence). The stratification variables will be included in the models as covariates.

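### The 80% power for the primary outcome holds at each time point separately, which the wording leaves unclear, and Holm's procedure would improve on the fixed 0.025 split with the same 76 schools

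*Protocol article*

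**What the plan says.** The Sample size section of the protocol article sets the size of the trial: "a sample of 76 schools (38 per arm) will provide 80% power to detect an absolute increase of ~ 35% between groups". What is compared is the share of schools that reach the four-practice target. Timing and alpha then appear together, the bracket giving the reason for the reduced alpha: "at 12 and 24-months (alpha 0.025 to allow for program effect at 12 or 24 months". The control proportion is assumed: "40% of schools in the usual care arm achieve this target at follow-up". Allocation is equal (Randomisation: "Block randomisation (1:1) will be undertaken within the strata").

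Under Statistical analyses, Primary outcomes, the two comparisons are modelled one by one: "Differences between treatment groups in the primary outcome at 12 and 24-months" are assessed with "a separate analysis conducted for each time point". That section names no significance threshold. The student-level calculation, also under Sample size, uses the same 80% and 2.5% and ties them explicitly to each follow-up taken separately.

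**The concern.** One sentence attaches 80% power to 12 and 24 months and justifies the alpha by 12 or 24 months. With two primary tests, three different powers can be meant: at one given time point, at both, or at one or more. They can differ by 20 points or more, and a reader who takes the and at face value would expect an 80% chance of showing the effect at both.

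The second issue is the method. A fixed 0.025 for each of two tests controls the family-wise error at 5% but gives up power. Once one null hypothesis is rejected at 0.025, the other can be tested at 0.05 without raising that error rate. With a ceiling of 76 schools, this is power that could be had without recruiting anyone.

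**Working it through.** **Inputs from the document.** n = 38 per arm, p1 = 0.40, p2 = 0.40 + 0.35 = 0.75, alpha = 0.025 per time point, two time points.

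**Assumptions.** Tests are two-sided (not stated, but one-sided 0.025 would give 88.6%, so two-sided fits the stated 80% better). The full 35-point effect is present at both times. No schools are lost. The correlation r between the 12- and 24-month test statistics is not given; the range 0 to 0.9 is shown.

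**Step 1: reproduce the plan's figure.** Pooled two-proportion formula, with pbar = 0.575:

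- standard error under the null = √(2 × 0.575 × 0.425 / 38) = 0.1134
- standard error under the alternative = √((0.40 × 0.60 + 0.75 × 0.25) / 38) = 0.1061
- alpha 0.025: b1 = (0.35 − 2.241 × 0.1134) / 0.1061 ≈ 0.903, power Φ(b1) = 81.7%
- alpha 0.05: b2 = (0.35 − 1.960 × 0.1134) / 0.1061 ≈ 1.204, power Φ(b2) = 88.6%

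The formula needs 37 per arm for 80%, so 38 per arm reproduces the plan as power for one test at one time point. Other approximations bracket it: exact power of the chi-square test 82.9%, Fisher's exact test 76.0%.

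**Step 2: joint powers.** Let Φ2(a, b; r) be the bivariate normal distribution function.

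- Fixed split, both: Φ2(b1, b1; r)
- Fixed split, at least one: 2Φ(b1) − Φ2(b1, b1; r)
- Holm, both (smaller p ≤ 0.025 and larger p ≤ 0.05): 2Φ2(b1, b2; r) − Φ2(b1, b1; r)
- Holm, a given time point: Φ(b1) + Φ2(b2, b1; r) − Φ2(b1, b1; r)

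By hand at r = 0:

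- both, fixed split: 0.8168² = 0.667
- at least one: 2 × 0.8168 − 0.667 = 0.966
- both, Holm: 2 × 0.8168 × 0.8857 − 0.667 = 0.780
- a given time point, Holm: 0.8168 + 0.8857 × 0.8168 − 0.667 = 0.873

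| Power (%) | r = 0 | r = 0.5 | r = 0.8 | r = 0.9 |
|---|---|---|---|---|
| Given time point, fixed split | 81.7 | 81.7 | 81.7 | 81.7 |
| Given time point, Holm | 87.3 | 86.3 | 85.4 | 84.9 |
| Both, fixed split | 66.7 | 71.0 | 75.0 | 76.9 |
| Both, Holm | 78.0 | 80.3 | 82.5 | 83.4 |
| At least one, either procedure | 96.6 | 92.3 | 88.4 | 86.4 |

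**Step 3: check on binary data.** Simulated school outcomes correlated between the two times and analysed with Pearson tests gave 83% at a given time point, 69-75% for both and 91-97% for at least one under the fixed split, and 78-82% for both under Holm.

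**Step 4: why Holm keeps the 5%.** If both nulls are true, a false rejection needs the smaller p ≤ 0.025, which has probability at most 0.025 + 0.025 = 0.05. If only one is true, rejecting it needs its own p ≤ 0.05. Whatever the fixed split rejects, Holm rejects too. The two procedures agree on whether anything is rejected at all, so power for at least one time point is identical.

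**The case against.** The strongest reply is that nothing is miscalculated. The and lists when the outcome is tested; the or explains why alpha is halved. The analyses are separate, and the student-level paragraph states its power for each follow-up separately. This reply stands: a reader might infer an arithmetic error or a firm contradiction, but the 80% reproduces and the per-time-point reading is the natural one. What remains is that the primary sentence does not say what the student sentence says plainly.

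A reader might also infer that the trial needs a win at both times and is therefore underpowered. No section makes success depend on both, and the stated reason for the alpha points to an effect at either time. If both were required, no split would be needed at all: testing each at 0.05 gives 78.5% (r = 0) to 85.1% (r = 0.9), slightly above Holm.

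It can further be said that 0.025 is only a planning alpha, that sizing on it does not rule out a later Holm analysis, and that the decision rule may sit in an analysis plan not shown here. That is fair, and the missing threshold under Primary outcomes is not held against the protocol. But 0.025 per time point is the only rule the article states, and a test on the same data that is never less powerful is available. Holm adds nothing to the chance of success at one or more time points; its gain is at each time point and at both.

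**Conclusion.** The 80% is correct as power at each time point separately; its label is ambiguous. It should not be read as the power for both (about 67-77%) or for at least one (about 86-97%). Holm gains roughly 3 to 6 points per time point (81.7% to 84.9-87.3%) and 6 to 11 points for both, with no more schools and no more type I error.

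The single-time-point power under the fixed split depends only on the plan's inputs, the two-sided reading and the pooled formula. The joint and Holm figures also depend on the unstated correlation and on a full 35-point effect at both times. The protocol says implementation builds over two school years, so the 12-month effect may be smaller; that would lower power for both under either procedure. If single-test power were exactly 80%, Holm would give about 75-82% for both. This is an inexpensive improvement and does not threaten the trial's validity.

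**What to change.** In Sample size, state that the 80% is the power at 12 months and at 24 months each taken separately, at two-sided alpha 0.025. If joint powers are given, add the assumed correlation range and the equal-effect assumption.

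In Statistical analyses, Primary outcomes, add the decision rule: compare the smaller of the two p-values with 0.025; if it passes, compare the other with 0.05. Fix this before the data are unblinded.

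The change is two sentences, with two small drawbacks. A 12-month p-value of 0.025 or less can be declared at once, but one between 0.025 and 0.05 counts only if the 24-month p-value proves to be 0.025 or less, so a 12-month report would have to leave it open. Confidence intervals matching a step-down test are less simple; 97.5% intervals at each time point can be shown alongside.

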### Trial discontinuation or modification

It is not anticipated that any events would occur that would warrant discontinuing the trial. Any unforeseen adverse events will be reported to the Hunter New England Human Research Ethics Committee (primary approval committee) and advice sought regarding required action. The trial registration record will be updated with any protocol modifications and any deviations from original protocol will be reported in study outcome papers.

## Discussion

Implementation research is a neglected area of scientific investigation, particularly within community settings [72]. Research evaluating methods for increasing implementation of effective health policies, programs or practices represents just 1% of health promotion research publications. [73] Similarly, recent systematic reviews have identified few implementation intervention trials across a variety of community settings and health behaviours, and a scarce number of implementation trials conducted at-scale [29, 72, 74]. Rigorous trials of theoretically based implementation interventions provide the best evidence to identify solutions to bridge this evidence-practice gap and assist in providing critical information needed to support implementation at scale. Scaling up effective public health interventions is the ultimate goal, as unless interventions are delivered at scale, they offer little benefit to population health [75]. This trial is one of few large-scale, randomised trials of an intervention to improve PA practice implementation at-scale in a non-clinical setting. Using a systematic, theoretically grounded approach, this trial will provide critical information to develop more efficient and effective next generation trials focused on implementation scaling-up and scaling-out.

This will be the first implementation study at-scale of a PA intervention targeting PA practices in socio-economically disadvantaged secondary schools. The findings will inform future efforts to support schools to implement health promoting policies and programs. Further, the findings could provide a basis for supporting implementation of other evidence based policies in this setting.

## Abbreviations

BMI: Body Mass Index
HPS: Health Promoting Schools
LOTE: Language other than English
MVPA: moderate-to-vigorous intensity physical activity
NSW: New South Wales
PA: Physical Activity
PA4E1: Physical Activity 4 Everyone
PE: Physical Education
